##### Turn-around time of infant test results

We will calculate the number of weeks between the date that the dried blood spot sample was collected and the date that the result was made available to the hospital. We will also calculate the time (in weeks) to notifying the mother of her infant’s test results.

##### Timely delivery of EID Services

For each of the 8 EID intervention points (Table 1), we will create an Optimal EID Care Index to measure whether the service was completed at all (1 point) or never completed (0 point) and whether it was completed on-time (1 point) or off-time (0 point). For each EID intervention point, each mother-infant dyad may receive either 0 point (never completed), 1 point (off-time completion), or 2 points (on-time completion). From these data, we will create an Optimal EID Care Index score for each dyad by summing across the 8 EID intervention point scores (range of 0–16 points). Dyads receiving a minimum score of 0 will have completed none of the 8 EID intervention points. Dyads receiving a maximum score of 16 will have completed all 8 points on-time. Scores between 0 and 16 will reflect some combination of completion and on-time completion.

#### Participant satisfaction

A sub-sample of mothers at all intervention and control sites (*n* = 30 per site) will complete satisfaction interviews when their infants are between 9 and 18 months of age. EID providers at each site and laboratory technicians at participating laboratories will also complete satisfaction interviews after 6–12 months of study implementation. Purposive sampling includes mothers with both HIV-infected and uninfected infants and those with and without mobile phones. Semi-structured surveys will elicit mothers’ experiences with the HITSystem and standard EID care. Satisfaction among EID providers and laboratory technicians will be assessed to identify perceived strengths and weaknesses, motivations and confidence to provide EID services, and recommendations to improve future EID outcomes.

#### Cost-effectiveness

We will evaluate the cost-effectiveness of the HITSystem from a “donor” or government perspective to evaluate integration of the HITSystem technology into an existing EID system. Cost data will be collected three times over the course of the study: 6, 18, and 30 months after intervention launch. A costing survey documents facility and laboratory related costs for commodities and services rendered and estimates low, medium, and high ranges for each type of expense. Relevant costing data from mothers is collected by the enrollment survey and again by the satisfaction surveys.

### Reimbursement

As a system-level intervention, all HIV-infected mothers and their HIV-exposed infants (mother-infant pairs) are eligible to participate. No remuneration is provided for enrollment in the HITSystem or completion of enrollment and satisfaction surveys. Satisfaction surveys are coordinated to coincide with scheduled appointments to avoid any additional transport burdens. Record review for cost-effectiveness analyses is conducted by study staff and thus do not require remuneration.

### Statistical analyses

We will calculate descriptive statistics to compare outcomes for each of the eight time-sensitive EID outcomes by intervention or control hospitals. In our preliminary analyses, we will estimate general linear models to determine whether there are pre-intervention differences across conditions and hospitals—for any of the measures we will be using as predictors or outcomes. Any significantly different variables will be included as covariates in our analytic models. Given attrition (not completing all 8 EID intervention points) is a major outcome of interest, we will predict and describe it. Hence, even “missing” or “lost” dyads will be included in outcome measures.

To predict patterns of EID utilization among HIV-exposed infants, we will first identify bivariate correlates of the main outcome: EID retention. Correlations between incomplete EID retention and possible predictors (e.g., infant sex, maternal disclosure, etc.) will be conducted and tested for significance using Phi, Point Biserial, or Spearman Rho statistics depending on the measurement level of each predictor. We will then include variables that are significantly correlated with EID retention in the generalized linear mixed model and use a stepwise approach to identify a parsimonious list of predictors, controlling for the correlation of observations within cluster with random effects. We will follow the same steps to assess correlates of the 5 unique EID intervention points that comprise the summative incomplete EID retention variable:(1) DBS not collected, (2) mother not notified of result, (3) HIV+ infant not started on ART, (4) HIV infant not re-tested at 9 months, and (5) HIV infant not re-tested at 18 months. To identify the most vulnerable time periods for EID retention, we will use survival analysis with random effects [23] to determine how long infants stay in EID care and identify time periods when significant drops in EID retention occur. Visual EID retention curves will illustrate differences in EID care retention at various time points throughout the 18-month EID period. Comparisons between intervention and control participants will highlight the impact of the HITSystem at various time points in EID utilization.

To assess the impact of the HITSystem on timely administration of eight critical EID interventions (Optimal EID Care Index), we will analyze data using multilevel modeling (Proc MIXED in the SAS System version 9.4) [24] to account for the nesting of time within dyad within hospital. This will increase the precision of treatment effect estimates by more correctly estimating standard errors (that are not correctly estimated when nesting is ignored) and indicate inferences about change over time by condition. We will include covariates that may be associated with EID completion (e.g., infant sex, distance from hospital, cell phone ownership) in addition to any pre-intervention differences identified across conditions and hospitals. Outcome variables of interest include an aggregate score and sub-scale scores (based on the Optimal EID Care Index), infant age at first PCR test, proportion re-tested by 9 months, and proportion re-tested by 18 months.

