## Methods/design

### Trial design

This is a 5-year phased cluster-randomized, controlled trial design to rigorously evaluate the impact of the HITSystem in Kenya. Study sites are six government hospitals in Kenya matched on geographic region, resource level, and patient volume to produce three-matched pairs. One hospital in each pair was randomly assigned to either the intervention (HITSystem) or control group (standard of care) condition; resulting in three interventions and three control study sites. We anticipate a 12-month window to complete enrollment of *n* = 120 mother-infant dyads per hospital, followed by an 18-month follow-up period (until end of Year 3). In Year 4 the HITSystem will cross over to initial control sites whose standard of care data from the 12 months prior will serve as a comparison for analyses.

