#### Retrospective data

Research Coordinators conducted a thorough retrospective record review of the EID Registry at each hospital to document EID outcomes (Table 1) during the 12 months prior to study implementation. Supporting medical records (described in the primary EID outcome section below) were used to complete missing data points in the EID Registry.

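### Covariates for the efficacy models are chosen by significance tests with no stated cluster term and no cap, although six hospitals leave arm only 4 degrees of freedom

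*Protocol article*

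**What the plan says.** All places are in the protocol article.

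- **The screen** (Statistical analyses, first paragraph): "we will estimate general linear models to determine whether there are pre-intervention differences across conditions and hospitals". Its scope is wide: "for any of the measures we will be using as predictors or outcomes". No random effect or other cluster term is named for these models, whereas random effects are named for the later retention and survival models.
- **The rule** (same paragraph): "Any significantly different variables will be included as covariates in our analytic models".
- **Where it leads** (third paragraph of the section): the multilevel model for the Optimal EID Care Index takes three example dyad covariates (infant sex, distance from hospital, cell phone ownership) and adds whatever the screen has found.
- **Baseline outcome data** (Retrospective data): registry records at each hospital were reviewed "to document EID outcomes (Table 1) during the 12 months prior to study implementation". No other pre-intervention outcome data are described, so these appear to be what the screen would test for outcomes.
- **Design** (Trial design): the six hospitals were "matched on geographic region, resource level, and patient volume to produce three-matched pairs", with one hospital of each pair in each arm.

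**The concern.** Under this rule the data decide what the treatment effect is adjusted for. Three things make that a poor choice here.

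1. A test on dyads that ignores hospital treats 720 correlated observations as independent. It will often call a measure different between arms when only ordinary hospital variation is present.
2. The comparison is also made across hospitals. Hospitals do differ, so with 120 dyads each such a test is significant for most clustered measures. It says little about whether the arms need adjusting.
3. The retrospective outcomes belong to infants born before the trial cohort. A trial dyad has no value of its own, so each such outcome enters as one number per hospital. With three hospitals per arm there is very little room for covariates of that kind, and the rule sets no limit.

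At stake are an efficacy model whose content is unknown until the data are seen and, if several retrospective outcomes are flagged, one that six hospitals cannot support.

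**Working it through.** The plan gives no figure for the screen, so there is none to reproduce.

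**Inputs.** From Power and sample size: 120 dyads per hospital, six hospitals, ICC 0.01 to 0.05, effect size 0.44, alpha 0.01. The screening level is not stated; 0.05 is assumed. The number of retrospective dyads per hospital is not given; 120 is assumed.

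**Step 1. Dyad-level test of condition, no hospital term, no true arm difference.** The design effect is DEFF = 1 + 119 × ICC, and the flag rate is 2 × [1 − Φ(1.96/√DEFF)].

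- ICC 0.05: DEFF = 6.95, 1.96/2.636 = 0.743, flag rate 45.7%.
- ICC 0.01: DEFF = 2.19, 1.96/1.480 = 1.324, flag rate 18.5%.

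**Step 2. Dyad-level F test across six hospitals (5 and 714 df).** Hospital variation multiplies the F ratio by k = 1 + 120 × ICC/(1 − ICC). The 5% critical value is 2.227, and the flag rate is P(F > 2.227/k).

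- ICC 0.05: k = 7.32, threshold 0.304, flag rate 91%.
- ICC 0.01: k = 2.21, threshold 1.007, flag rate 41%.

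**Step 3. Room at hospital level.** Six hospital values less intercept and arm leave 4 df. With q hospital-level covariates, 4 − q remain: 3, 2, 1, 0 for q = 1 to 4. A fifth gives more parameters than hospitals. Table 1 lists eight outcomes. If each had these ICCs and 120 retrospective dyads, the expected number flagged would be:

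| Test | ICC 0.01 | ICC 0.05 |
|---|---|---|
| by condition | 8 × 0.185 = 1.5 | 8 × 0.457 = 3.7 |
| across hospitals | 8 × 0.41 = 3.3 | 8 × 0.91 = 7.3 |

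This is only an illustration; ART initiation, for example, applies to infected infants alone.

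**Step 4. What one fixed hospital-level covariate would do (ICC 0.05, effect 0.44).** Unadjusted, a hospital mean has variance 0.05 + 0.95/120 = 0.0579. The SE of the arm difference is √(2 × 0.0579/3) = 0.196, the noncentrality is 0.44/0.196 = 2.24, and power with 4 df is 40% at two-sided alpha 0.05 and 13% at 0.01. With the hospital's retrospective value added (3 df), power was simulated so as to include the cost of estimating the slope from six hospitals and the sampling error of the baseline. The documents give no correlation over time, so three values are assumed.

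| Hospital-level correlation | Power, alpha 0.05 | Power, alpha 0.01 |
|---|---|---|
| unadjusted | 40% | 13% |
| 0.5 | 33–34% | 9% |
| 0.8 | 47% | 14–15% |
| 0.9 | 57% | 19% |

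The unadjusted values are below the plan's stated 80%. That is a separate question, and this point does not depend on it.

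**The case against.** Much can be said for the plan, and most of it stands.

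- **The 91% is not a false-positive rate.** At ICC 0.05 the hospitals truly differ and the test finds that. This stands. It also shows that the test does not identify arm imbalance.
- **The 46% assumes a pooled test.** The article does not say how hospital enters the general linear models. If condition were tested against between-hospital variation, the rate would be the nominal 5%. The rule would still be data-driven and uncapped.
- **Stepwise selection.** A reader might infer that it shapes the efficacy model. It does not. The phrase "use a stepwise approach to identify a parsimonious list of predictors, controlling for the correlation of observations within cluster with random effects" belongs to the prediction of retention, which the Background lists as a secondary outcome, and it runs inside a mixed model. The preceding Phi, point-biserial and Spearman screen does ignore clustering, but mildly: simulated flag rates are 4.7% to 16.8% at nominal 5%. Nor is retention left without an arm comparison: a survival analysis with random effects and the re-test proportions in the multilevel model both provide one.
- **Baseline data left out.** A reader might infer this too. The screen covers outcomes, so the retrospective data can enter. The weakness is that entry depends on a test.
- **Standard errors too small.** This is not shown. Simulating screen-then-adjust with one dyad-level covariate and a 4-df test gave type I error of 4.1% to 5.6% at nominal 5%. Dyad-level covariates use no hospital df, so the saturation problem is confined to hospital-level ones.
- **Most of the precision thrown away.** The formula SE = √(2 × [0.05(1 − r²) + 0.95/120]/3) with 3 df gives power of 42%, 62% and 77% at r = 0.5, 0.8 and 0.9. It omits the slope and baseline-sampling costs in Step 4, so it overstates the gain.
- **No pair term.** This is a defensible choice. Fixed pairs cut df from 4 to 2; at ICC 0.05 and alpha 0.05, power is 26%, 38% and 49% at assumed pair correlations of 0, 0.5 and 0.7, against 40% without.

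**Conclusion.** The point holds in a limited form. The plan states a significance rule for covariates of the efficacy model, covering predictors and outcomes, with no cluster term named and no cap. Run on dyads without a hospital term, the screen would flag 19% to 46% of measures with no true arm difference by condition, and 41% to 91% across hospitals, over the plan's own ICC range. These rates rest on the assumed 0.05 screening level and on that reading of the general linear models. The structural problem needs neither assumption: retrospective outcomes can act only at hospital level, arm has 4 df there, and four flagged outcomes would exhaust them. No bias or type I error inflation in the treatment test has been demonstrated, and degrees-of-freedom methods may properly be left to the analysis plan, which is not shown. The change is worth making because the rule is stated outright and replacing it is cheap.

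**What to change.** Delete the significance rule. For each primary outcome, fix one model in advance with:

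- arm, always included;
- a hospital random effect;
- the dyad covariates already named in Statistical analyses (infant sex, distance from hospital, cell phone ownership), as a closed list and not as examples;
- at most one hospital-level covariate: that hospital's retrospective 12-month value of the same outcome.

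Say explicitly that stepwise work serves only the secondary predictor aim. A matched-pair term is optional; state whether it is used.

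**Cost.** This is a change of wording. The retrospective data are already collected, and Trial status reports that no analyses had been run. The hospital-level covariate is not free: it takes one of the 4 df and, on the figures above, loses power at a correlation of 0.5 and gains at 0.8 or more. Whether to include it should therefore be decided beforehand, from what is known about how stable hospital performance is, and not from a test in the trial data.

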Our study aims to evaluate the HIV Infant Tracking System (HITSystem), a web-based tool designed to address many of the barriers in current EID service provision in Kenya, with the ultimate goal of maximizing the quality of EID services. As a system-level intervention, it was not deemed feasible or acceptable to randomize at the individual level; therefore, randomization occurred at the site (hospital) level. Primary outcomes will be measured at the participant (mother-infant dyad) level and aggregated to report outcomes per hospital. The primary outcomes for efficacy of the HITSystem are retention through the EID Cascade of Care (measured by eight unique benchmarks between 0–18 months postnatal, including ART initiation among HIV-infected infants) (Table 1) and efficiency of services (turn-around times for EID services and ability to meet age and time-specific targets with the HITSystem compared to control sites where standard of care services are provided). Secondary outcomes are maternal and infant predictors of retention, postnatal period(s) at the highest risk for loss to follow-up, satisfaction among mothers and providers, and infant HIV infection status over time. Cost-effectiveness analyses will quantify resources required to implement the HITSystem versus standard EID services and calculate potential short and long-term costs averted by this intervention to inform scale-up and sustainability.

**Table 1 Tab1:** HITSystem targets: eight time-sensitive EID interventions

1.Initiation of OI prophylaxis at 6 weeks
2.Collect dried blood spot (DBS) for PCR test by 6 weeks
3.Receipt of DBS at lab within 10 days of collection
4.Return of PCR results from lab within 2 weeks
5.Notify mother within 2 weeks of the EID provider receiving results
6.Initiate all HIV-infected infants on ART within 4 weeks of notifying the mother
7.Retest all HIV-uninfected infants at 9 months, initiate ART w/in 4 weeks if applicable^a^
8.Retest all HIV-uninfected infants at 18 months, initiate ART w/in 4 weeks if applicable^a^

^a^Re-testing indicated at these time points or 6 weeks after cessation of breastfeeding

Greater detail regarding the 8 intervention points and the HITSystem process has been previously published. [21]

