### Standard of care

The current standard of care (SOC) for EID in Kenya has many well-documented challenges [8, 10, 11, 17]; however, when effectively implemented as designed, the following should take place: The EID provider should gather information on relevant maternal and infant clinical and demographic data at the time of postnatal enrollment in EID. These data should be entered in a large paper registry book (HIV-Exposed Infant Registry), organized by month of birth. Dried blood spot samples should be collected at the targeted age of 6 weeks and sent via courier to the central laboratory for processing. The samples should then be processed at the lab and paper polymerase chain reaction (PCR) test results returned to the hospital via courier and then sent to MCH to be added to the mother-infant file and recorded in the EID registry. If the infant has an HIV-positive test result, EID staff should contact the mother via phone to ask her to return to the clinic where she should be counseled about the HIV-positive result and referred to the Comprehensive Care Center (CCC) where a first line pediatric ART regimen should be initiated [6, 20]. If the result of the initial PCR test is negative, the result should be noted in the paper registry and the mother should be informed at a subsequent clinic visit and advised to return with the infant for a re-test at 9 months of age. At 9-months postnatal, all HIV-exposed infants should receive an antibody test, and if positive, a confirmatory PCR test should be conducted using the previously described process for PCR testing. If the antibody result is negative, the mother should be asked to return 6 weeks after the cessation of breastfeeding or when the infant is 18 months old to repeat this process. Even when implemented as designed, the current SOC for EID has multiple gaps where mothers often fall out of care, employ extremely limited prospective tracking to identify when services are indicated, and rely on a passive system for communicating test results to mothers. These shortcomings combined with well-documented challenges involving delayed or lost samples resulting in long turn-around time for infant test results combine to produce the observed poor retention and completion rates [8, 10, 11, 17].

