The HITSystem tracks the care of infants enrolled in EID so that those who drop out of care can be easily identified and targeted for outreach. Using the infant’s date of birth, the HITSystem configures automated electronic alerts for eight time-sensitive interventions to optimize care for HIV-exposed infants. The order and timing of these action alerts have been previously published [21]. PCR test results entered into the online system from the lab become available to hospitals in “real time” thus eliminating the need for costly and unreliable couriers to transport paper results. Excessive delays for laboratory test results are also targeted by triggering alerts at the laboratory for samples received but not tested within 10 days. When results are available, mothers are sent an Short Message Service (SMS) message asking them to come to the hospital at their earliest convenience. Text messages do not relay sensitive information that could compromise confidentiality. In the case of indeterminate results, mothers are notified to return with infants to collect another sample. To address one of the weakest areas of current EID care, the HITSystem proactively texts mothers when re-testing of infants is due at 9 and 18 months of age. Infants enrolled in the HITSystem are tracked until they are either (a) conclusively determined HIV negative at 18 months and discharged from EID, (b) determined to be HIV-infected, initiated on ART, and linked to pediatric HIV care, or (c) dead or transfered to another health facility.

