##### EID retention

EID retention will be characterized as complete or incomplete. Incomplete EID care (loss to follow-up) is defined as one or more of the following: (1) DBS not collected, (2) mother not notified of result, (3) HIV-infected infant not started on ART, (4) HIV-uninfected infant not re-tested at 9 months, and 5) HIV-uninfected infant not re-tested at 18 months.

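### EID retention, the main outcome, is defined in two incompatible ways, and each, read as written, counts some correctly managed infants as lost

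*Protocol article*

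**What the plan says.** The Background names as a primary outcome retention through the cascade, "measured by eight unique benchmarks between 0–18 months postnatal, including ART initiation among HIV-infected infants", and lists the eight in Table 1. Point 6 (starting ART) concerns infected infants. Points 7 and 8 (re-tests at 9 and 18 months) concern uninfected infants.

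The EID retention section classes each dyad as complete or incomplete: "Incomplete EID care (loss to follow-up) is defined as one or more of the following". Five failures follow: no DBS collected, mother not told the result, infected infant not on ART, uninfected infant not re-tested at 9 months, and uninfected infant not re-tested at 18 months.

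Statistical analyses contains both versions. It first says "Given attrition (not completing all 8 EID intervention points) is a major outcome of interest". It later calls EID retention the main outcome and refers to the "5 unique EID intervention points that comprise the summative incomplete EID retention variable".

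Four other places bear on the five criteria:

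- Table 1, footnote a, on points 7 and 8: "Re-testing indicated at these time points or 6 weeks after cessation of breastfeeding".
- Standard of care: after a negative 9-month antibody test the mother is asked to "return 6 weeks after the cessation of breastfeeding or when the infant is 18 months old".
- Participant eligibility and consent: infants may enrol at any age under 18 months.
- HIV infant tracking system: tracking also ends when the infant is "dead or transfered to another health facility".

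Statistical analyses also lists the proportion re-tested by, rather than at, 18 months.

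**The concern.** A trial needs one rule for its main outcome. Here one section holds two, and they can disagree about the same dyad. The five criteria omit OI prophylaxis, receipt of the DBS at the laboratory and return of the result (points 1, 3 and 4). A dyad whose only gap is OI prophylaxis is therefore retained under one rule and lost under the other.

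Neither rule, taken literally, separates infants who dropped out from infants who received everything that applied to them. Statistical analyses keeps lost dyads in the outcome, so such misclassification enters the primary comparison directly. If the choice is left until data are seen, it becomes a choice among versions of the primary outcome.

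**Working it through.** The document gives no figure to reproduce, because this is a matter of definition. The check takes each infant pathway with all indicated care given, counts the Table 1 points that can be completed at all (ignoring timeliness), and asks whether any of the five criteria is triggered.

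| Pathway | Points attainable | Count of 8 | Five criteria |
|---|---|---|---|
| Uninfected throughout | 1–5, 7, 8 | 7 | complete |
| Infected at first PCR, on ART | 1–6 | 6 | complete |
| First positive at 9 months, on ART | 1–5, 7 (and 6 if it covers any ART start) | 6 (or 7) | complete |
| First positive at 18 months, on ART | 1–5, 7, 8 (and 6 if it covers any ART start) | 7 (or 8) | complete |
| Uninfected, 9-month re-test, closing re-test 6 weeks after breastfeeding, before 18 months | 1–5, 7 | 6 | lost (fifth criterion) |
| First enrolled after 9 months, uninfected, re-tested at 18 months | 1–5, 8 | 6 | lost (fourth criterion) |
| Uninfected, 9-month re-test, transferred at 12 months | 1–5, 7 | 6 | lost (fifth criterion) |

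An uninfected infant who dies between the 9- and 18-month re-tests is scored like the last row.

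**All-eight rule.** Every row fails except, on the broad reading of point 6, the infant first positive at 18 months.

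**Five criteria.** The first four rows are complete, because these criteria are conditional on HIV status. The last three are lost, although footnote a and Standard of care, the eligibility section, and the tracking section respectively allow for them.

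**Could the arms differ?** Standard of care mentions the breastfeeding route, while the tracking section describes texts at 9 and 18 months. Suppose true retention R is equal in both arms and a share q of correctly completed controls, but no HITSystem infants, had an early closing re-test. The spurious difference is then R × q. The document gives no value for q, so both inputs are assumptions:

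- R = 0.40, q = 0.05: 0.40 × 0.05 = 0.02, or 2 percentage points.
- R = 0.75, q = 0.20: 0.75 × 0.20 = 0.15, or 15 percentage points.

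This range shows only what the mechanism could do if it operated in one arm alone. It is not an estimate.

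**The case against.** The best defence is that the working definition is clear. The EID retention section states the five criteria, Statistical analyses repeats them, and the all-eight wording is one loose parenthesis. The Background says retention is measured by eight benchmarks, not that all must be met, and its mention of ART among infected infants shows that benchmarks are conditional. This largely stands: the five criteria are probably what is intended, and the Background is not a second all-eight rule. But the parenthesis defines attrition in the analysis section, in a passage explaining why lost dyads stay in the outcome, so it has to be changed.

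A second defence is that the 9- and 18-month criteria inherit footnote a, and that the re-tested-by-18-months wording would credit an earlier test. That is a plausible intention, but the criteria do not say so. Three wordings of one requirement need reconciling.

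A third is that death, transfer and late enrolment are details for an analysis plan, and that reason for discharge is collected. Collecting the reason does help. However, the published rule is not merely silent: any one unmet criterion makes the dyad incomplete, with no exemption.

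A reader might also infer that early re-tests are scored as loss mainly at control sites, so that the outcome favours the HITSystem. The document does not support that. Footnote a belongs to the table of the HITSystem's own targets, the detailed alert timing is left to a cited publication, and Primary EID outcomes describes parallel assessment with the same outcomes measured at all sites.

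**Conclusion.** The point holds. Statistical analyses contradicts both the EID retention section and itself on the main outcome. The all-eight version fails every uninfected infant and every infant infected at first PCR, however well managed. The five-criterion version is workable, but as written it misclassifies early closing re-tests, enrolments after 9 months, and deaths and transfers.

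It would go too far to say that nobody could be complete, or that completion would be 0% in both arms: an infant first positive at 18 months could reach 8 if point 6 covers any ART start. The direction and size of any difference between arms are not established, because the document gives no rates for the affected pathways. The conclusion rests on reading the criteria literally and does not depend on the 2 to 15 point illustration.

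**What to change.** - Make the five-criterion definition in the EID retention section the only definition of retention, and replace the all-eight parenthesis in Statistical analyses. Keep the eight points as separate benchmarks and for the Optimal EID Care Index.
- Score each criterion only if it fell due while the infant was enrolled, alive and not transferred.
- Reconcile the re-test timing across Table 1 and its footnote, Standard of care, HIV infant tracking system, EID retention and Statistical analyses. Which schedule is right is for the investigators. Whichever is adopted, score re-tests by that one rule identically in both arms.
- Report death and documented transfer separately, with a sensitivity analysis counting them as not retained.

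This changes scoring only, and Trial status says no analyses have been conducted. The cost is wording and some extra programming. If the reconciled rule uses the end of breastfeeding, that date must be read from records where noted. It is not among the HITSystem outputs listed in Primary EID outcomes, so its completeness should be compared between arms, since unequal recording could itself misclassify by arm.
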